## Abstract

**Introduction:**

Nearly 80% of healthcare providers experience adverse psychological symptoms (e.g., depression, burnout, sleep disturbance) stemming from workplace stressors. Elevated levels of stress have been associated with unfavorable occupational, patient, and provider-related outcomes, imposing a heavy burden on a strained system. Given the impact of stress on both employee and patient health, effective interventions are urgently needed to reduce distress and promote well-being among healthcare professionals. Mindfulness-based interventions show promise for addressing these challenges. We developed a six-week, remotely delivered mindfulness intervention, the Building Emotional Strength Training (BEST) program, based on the Buddhist Four Immeasurables practice to cultivate the distinct emotional qualities of loving-kindness, compassion, joy, and equanimity. The present study aims to evaluate the feasibility and efficacy of a Four Immeasurables-based mindfulness intervention on perceived stress (primary outcome), burnout, depressive symptoms, and inflammatory biomarkers, while enhancing psychological well-being and sleep quality (secondary outcomes) in physicians. We will also investigate potential mediators of intervention effects, including compassion, positive affect, equanimity, and mindfulness.

**Method:**

We will enroll 90 full-time physicians in a remote, two-arm randomized controlled trial with 1:1 allocation to either the meditation intervention or waitlist control. Participants will complete self-report questionnaires and provide blood samples at baseline, mid-course, and post-intervention to assess outcomes and mediators.

**Discussion:**

The project aims to advance the study of mindfulness-based interventions that reduce distress and promote well-being through practices that cultivate prosocial and altruistic feelings toward oneself and others. While mindfulness interventions have gained considerable interest, none have specifically drawn from the Four Immeasurables practice to target loving-kindness, compassion, joy, and equanimity. This novel investigation could expand our understanding of practices that foster kindness and compassion to reduce distress in an at-risk population.

**Trial registration:**

ClinicalTrials.gov NCT07283744, registered on 2025/10/14. The Open Science Framework, registered on 2026/06/26.

## Introduction

Healthcare providers face a large number of stressful situations daily, which may increase their risk of developing adverse mental and physical health conditions [1–4]. Downstream consequences of working in high-stress healthcare occupations include elevated levels of stress, depressive symptoms, and burnout. It is estimated that frontline healthcare workers, including physicians, experience higher rates than the general population of stress, depression [3,5], and burnout [6–9]. These conditions have been associated with unfavorable occupational [10–22], provider [23–28], and organizational outcomes [10,17,29–31]. Among healthcare workers, physicians face a distinct constellation of stressors, including high decision-making and diagnostic burden [32], long and irregular hours [33], and a lack of organizational support [32,33], that may not be fully addressed by interventions developed for the broader workforce.

In addition to the occupation-specific outcomes associated with increased levels of distress, growing evidence suggests that stress exposure can influence physical and mental health-related outcomes (e.g., cardiovascular disease, diabetes, depression, etc.) by stimulating pro-inflammatory biology [34–36]. In fact, frontline healthcare workers experience high rates of physical complaints [1,2,37–41] that may be due to elevated inflammatory activity. Additionally, elevated inflammation may adversely affect cognitive, emotional, and behavioral outcomes [42–44], further impairing healthcare providers’ effectiveness.

Although much of the literature identifies organizational and structural factors, such as workload, administrative burden, and scheduling, as central drivers of physician stress and burnout [33], individual-level interventions may offer complementary tools that help physicians manage the distress these conditions produce [45]. To date, several attempts have been made to address psychological distress among healthcare providers using individual-focused behavioral interventions, with mixed results [45–48]. Given the encouraging effects of mindfulness-based interventions (MBIs) on various outcomes in diverse populations [49,50], it is unsurprising that these interventions have been used to address the needs of healthcare workers. Recent reviews have investigated the effects of several MBIs on various outcomes in healthcare provider populations with mixed results. Meta-analytic data suggest that while Mindfulness-Based Stress Reduction (MBSR) has demonstrated beneficial effects on reducing experiences of anxiety, depression, and perceived stress, the intervention was not effective at reducing symptoms of burnout [51]. These results may suggest that the specific type of mindfulness practice may matter for addressing the distress physicians experience. Interventions drawing on diverse contemplative practices (e.g., loving-kindness and compassion-based) remain largely unexamined in this population. Because physicians face substantial time and scheduling constraints, remote delivery may also improve the feasibility and reach of such interventions [52].

One of the ultimate goals of many MBIs, including MBSR, is to familiarize participants with what it means to be aware (i.e., mindful). Thus, the practices included in the interventions are designed to strengthen one’s ability to recognize when their awareness has drifted from the present moment and how to bring their focus back to the here and now [53]. An intervention aimed at enhancing positive psychological states may be more effective at reducing distress in this population. One such meditation-based intervention is the Four Immeasurables, also known as the Brahmaviharas in Pali.

The Four Immeasurables were described in the Fifth Century in one of the primary treatises on Buddhist practice, the Visuddhimagga [54], and include the distinct emotional qualities of loving-kindness, compassion, sympathetic joy, and equanimity [55]. These emotional states are gradually cultivated through specific practices that often include visualizing oneself and others and directing the feeling state of the particular component (e.g., loving-kindness) to one’s target by mentally reciting phrases such as “may you live with ease.”

Although the Four Immeasurables have been practiced in traditional Buddhist settings for thousands of years, the entire four-factor program has not been investigated in a randomized controlled trial (RCT). Despite a shortage of trials investigating the complete Four Immeasurable practice, there is evidence from RCTs evaluating interventions that include singular components of the Four Immeasurables, as well as from cross-sectional studies demonstrating the benefits of experiencing kindness, compassion, joy, and equanimity. These investigations suggest that these practices and emotional states can beneficially impact psychological, social, and biological outcomes [56–64]. Additionally, these four psychological constructs may be particularly beneficial in lessening the common occupation-related symptoms experienced by healthcare providers, namely perceived stress, depression, and burnout [60,65,66]. Furthermore, the favorable social influences that the Four Immeasurables appear to foster [60,67,68] may suggest that these practices would significantly benefit individuals in caregiving occupations, thereby improving patient outcomes and enhancing provider well-being.

### Objectives and aims

Our team has developed a manualized mindfulness intervention, the Building Emotional Strength Training (BEST) program, based on the traditional Four Immeasurables practice to reduce stress among physicians. In this article, we describe the protocol for a single-site, two-arm, parallel-group RCT evaluating the feasibility and efficacy of the BEST intervention, delivered remotely, compared with a waitlist control (WLC) for perceived stress among physicians. Ninety physicians with elevated stress will be randomized to BEST or a WLC condition. Aim 1 is to assess the feasibility of delivering the BEST intervention in a workplace setting to full-time healthcare workers. Aim 2 is to determine the effects of BEST vs. WLC on perceptions of stress (primary outcome). Aim 3 is to evaluate the effects of BEST vs. WLC on negative (depressive symptoms and burnout) and positive psychosocial symptoms (psychological well-being and sleep quality; secondary outcomes) experienced by healthcare workers. Aim 4 is to determine the effects of BEST vs. WLC on inflammatory processes associated with stress and relevant to long-term health. Lastly, an exploratory aim will examine theoretically based mechanisms (compassion for oneself and others, positive emotions, equanimity, and mindfulness) of the effect of the BEST intervention on the primary outcome, perceived stress.

## Methods

The study flow and procedures are detailed in Figs 1 and 2. The trial was registered on ClinicalTrials.gov (NCT07283744) before recruitment, specifying the study design, arms, eligibility criteria, and primary and secondary outcomes. The detailed analysis plan was subsequently registered on the Open Science Framework (OSF; osf.io/npcax) before any access to outcome data. This trial has received Institutional Review Board (IRB) approval from the University of California, Los Angeles IRB (IRB-25–1518) and will be conducted and reported in accordance with CONSORT guidelines [69]. Any adverse or serious events will be reported to the principal investigators and the institutional review board within 24 hours.

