### Participants

Eligibility criteria include: 1) currently practicing physician (M.D. or D.O.), 2) at least 18 years of age, 3) willing and able to attend the six-week intervention, 4) fluent in English, 5) access to the internet and email, and 6) score of four or greater on the four-item Perceived Stress Scale [PSS-4; 70]. Perceived stress will be assessed using the PSS-4 during the initial phone screening. Exclusion criteria include: 1) having a current and consistent meditation practice (i.e., engaging in a formal meditation practice at least three days per week for five minutes each day), 2) previous participation in a Four Immeasurable course (e.g., attending a Brahmaviharas meditation retreat), 3) regular tobacco use (given its impact on immune function; [70]). Eligibility is intentionally broad to enhance generalizability to the physician population. We do not exclude participants on the basis of medical or psychiatric conditions or medication use. We do, however, assess these characteristics at baseline. Participants report current medication use (including dosage, frequency, and reason for use) and provide information on any diagnosed psychiatric conditions, use of mental health services, and the frequency of such use. These data are collected to characterize the sample and are available for use in sensitivity or exploratory analyses.

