As reviewed above, the traditional Four Immeasurables practice includes exercises designed to cultivate the distinct emotional states of loving-kindness, compassion, sympathetic joy, and equanimity. While the core practices are not altered, BEST incorporates light contextual adaptations for physicians, including content, examples, and informal practices framed in the language of clinical work (e.g., attending to a patient’s breath through a stethoscope as a cue for mindful awareness). The goal is to provide tools that can be deployed as needed in daily activities, especially during clinical duties. The BEST curriculum is a six-week program delivered in six weekly, one-hour, group-based videoconference sessions, each focused on a different component of the Four Immeasurables practice. Participants who attend at least three of the six BEST sessions will be considered to have completed the intervention. The practices introduced across BEST—mindfulness, loving-kindness, compassion, equanimity, and joy—each have independent empirical support for beneficial effects [50,60,75]. While the full program is designed to be delivered in its entirety and its components may confer additive benefit, the individual-level evidence indicates that even partial attendance exposes participants to practices with demonstrated value. Attending at least three sessions therefore represents a meaningful level of exposure rather than a negligible dose, supporting three of six as an adherence threshold. This threshold, consistent with prior work [76–78], is pre-specified to characterize intervention completion and to define the per-protocol sample in sensitivity analyses; it does not imply that partial attendance confers the full benefit of the complete program.

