During each session, participants receive structured training and instruction in meditation exercises, including theoretical background, formal guidance on the day’s topic, and question-and-answer sessions to support learning. Additionally, participants will be guided through each meditation exercise introduced during class. Furthermore, each class will include dyadic discussions, allowing participants to interact directly with one another. The sessions will introduce the following topics and associated practices: 1) introduction to mindfulness, 2) mindfulness and self-compassion, 3) self-directed kindness, 4) compassion, 5) equanimity, and 6) joy. The BEST intervention also includes home practice, in which participants are encouraged to practice the meditation technique introduced in class at home, starting with five minutes and gradually increasing to 20 minutes per day throughout the six weeks of the intervention. All sessions will be delivered by the intervention developer, who has nearly 30 years of experience teaching meditation.

*Waitlist Control (WLC).* The WLC will control for naturally occurring changes in the outcomes and mediators over the assessment period. Participants in this group will not engage in any study-related activities outside of the remote assessments (baseline, mid-course, and post-intervention). Participants randomized to this condition will be offered the BEST intervention after all data collection is completed.

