### Measures

Reliable, valid, and commonly used self-report questionnaires will be administered at baseline (T1), mid-course (T2), and post-intervention (T3) to assess participant characteristics and outcomes. All measures have been validated in adult populations and have been shown to be sensitive to the effects of psychosocial interventions. Questionnaires will be administered online using a Qualtrics link emailed to each participant. The complete list of measures is presented in Table 1.

**Table 1 pone.0357906.t001:** Assessment Schedule.

	T1	T2	T3

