**Background characteristics**			
Demographic characteristics	X		
Employment	X		
Health history, Use of mental health services	X		X
Height and weight measurements	X		
Health behaviors/meds	X		X
Calendar Allocation and Continuing Medical Education Training			X

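### No listed measure asks about adverse events and only BEST has live contact, so counts of spontaneously reported events by arm would be open to ascertainment bias of unknown size

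*Protocol article*

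**What the plan says.** The opening paragraph of Methods sets the rule for harms: "Any adverse or serious events will be reported to the principal investigators and the institutional review board within 24 hours". This fixes how quickly a known event is passed on. It does not define an event or say who asks about it, when, or in which arm.

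Under Measures, the article says: "The complete list of measures is presented in Table 1". That table has no row for adverse events. Under Procedures and study flow, the mid-course assessment (T2) is restricted to the primary outcome and the mediators.

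Contact differs by arm. Under Intervention conditions: "The BEST curriculum is a six-week program delivered in six weekly, one-hour, group-based videoconference sessions". For the waitlist: "Participants in this group will not engage in any study-related activities outside of the remote assessments".

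Some health information is collected on one schedule for everyone. Table 1 lists "Health history, Use of mental health services" and "Health behaviors/meds" at T1 and T3, the CES-D and ISI at T1 and T3, and the PSS at T1, T2 and T3. Of the baseline medication and mental-health data, the Participants section says: "These data are collected to characterize the sample and are available for use in sensitivity or exploratory analyses". Data management and monitoring states that there is no data monitoring committee, citing a low expected risk of serious events and short follow-up.

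**The concern.** A reporting deadline acts only on events that someone already knows about. If no survey asks, an event is likely to be known because a participant mentioned it, and BEST participants have far more occasions to do so. A count by arm would then partly measure contact.

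This matters here because the trial selects physicians for elevated stress, does not exclude psychiatric conditions, and describes itself as the first test of the full four-component practice. Readers of the results will want to know whether anyone got worse. An excess in BEST could reflect closer observation, and a low count in both arms could reflect events that nobody asked about. In either case the premise of low risk would be poorly tested.

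**Working it through.** The article gives no adverse-event rate, safety sample size or planned comparison of events, so there is no stated figure to reproduce. The check has two parts.

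**Routes by which an event could surface after baseline, as written**

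| Route | BEST | Waitlist |
|---|---|---|
| Live sessions | 6 | 0 |
| T2 emailed survey, perceived stress and mediators only | yes | yes |
| T3 emailed survey, includes health history, service use, medication, CES-D, ISI, PSS | yes | yes |
| Survey item asking about adverse events | none listed | none listed |

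The structured data are symmetric. The asymmetry lies in unprompted reports.

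**Illustration of size**

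Inputs from the article: 45 participants per arm, and about 72 of 90 expected to give complete outcome data (36 per arm if split equally). Assumed, because the article gives no values: the same true event rate p in both arms, and capture probabilities c_B in BEST and c_W in the waitlist.

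Expected observed events are 45 × p × c. With equal p, the apparent ratio is c_B / c_W whatever the value of p. Taking p = 10% and c_B = 90%, BEST shows 45 × 0.10 × 0.90 = 4.05 events, against:

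| c_W | Waitlist events | Apparent ratio |
|---|---|---|
| 90% | 4.05 | 1.00 |
| 70% | 3.15 | 1.29 |
| 50% | 2.25 | 1.80 |
| 30% | 1.35 | 3.00 |

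At p = 5% or 20% the counts halve or double and the ratios stay the same.

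If no events are seen in n participants, the one-sided 95% upper limit on the observable rate is 1 − 0.05^(1/n):

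- n = 45: 1 − 0.05^(1/45) = 6.4%
- n = 36: 1 − 0.05^(1/36) = 8.0%

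With incomplete capture, the limit on the true rate is this value divided by c. For n = 45 it is 6.4% / 0.5 = about 13% at 50% capture, and 6.4% / 0.3 = about 21% at 30% capture.

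Conversely, at p = 10% and c_W = 30%, the chance that the waitlist shows no events at all is (1 − 0.03)^45 = 25%.

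**The case against.** The strongest reply is that this is a condensed article. How events are elicited commonly sits in the full protocol or the IRB file, neither of which is shown. The sentence about Table 1 closes a paragraph on questionnaires, so it does not rule out an adverse-event log. This stands against one tempting inference, that events are captured only if someone volunteers them: the article nowhere says so. It does not dispose of the point. A survey item held elsewhere would conflict with the description of Table 1 and, at T2, with the stated restriction on content. Any other route for the waitlist would have to fit within the remote assessments.

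Second, no between-arm comparison of adverse events appears among the aims, outcomes or analyses. A reader might infer that the trial's harms comparison is biased, but the article plans none. The concern is with how counts by arm would be read if reported.

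Third, much relevant information is collected alike in both arms, and the outcome tests are two-sided, so average worsening on stress, depression, insomnia or burnout would show in the planned models. The analysis plan also records reasons for discontinuing where possible and reports reasons for missing outcome data by condition. All of this stands. A mean difference can still hide a few participants who deteriorate, and the article does not designate these data for a harms summary. It would be wrong, though, to say that it confines the health data to describing the sample: the Participants section expressly allows exploratory use.

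Fourth, the capture rates are invented. That is correct. They show a possible range, including no distortion at all, and do not estimate the bias.

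**Conclusion.** The point holds in a limited form. The article gives an onward-reporting rule and lists no adverse-event item, while live contact is six sessions against none. Spontaneous reports therefore have unequal opportunity to surface, and counts by arm would be open to ascertainment bias. The apparent ratio is about 1 to 3 under the assumed capture rates. That range takes capture in BEST to be at least as good as in the waitlist, which is plausible given the extra contact but is not established by the article.

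It would go too far to call a report of few events uninformative. With full capture, zero of 45 still bounds the rate at 6.4%. It is weak reassurance, and weaker the lower the capture. The primary and secondary efficacy analyses are unaffected.

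**What to change.** (a) For cohorts still to be assessed, add one short item with identical wording to the T2 and T3 surveys in both arms, asking about any new or worsened symptom or event since the last assessment and whether it led to stopping. Tabulate it by arm among those who were asked, with that denominator shown. List spontaneous reports separately, without comparative inference. If a common inquiry already exists in the full protocol, the article should say so and bring its account of Table 1 and T2 into line.

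(b) For all cohorts, before outcome data are accessed, pre-specify a descriptive by-arm summary from data already scheduled: new mental-health-service use and new medication between T1 and T3, the number whose CES-D, ISI or PSS worsened from T1 to T3 (with worsening defined in advance), and reasons for discontinuation.

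Part (b) needs no new data. Part (a) costs about one extra minute per survey and a minor IRB amendment. Recruitment began in December 2025 in cohorts of 20 to 30, with data collection to December 2026, so participants who have already finished will have no solicited item and only (b) will cover the whole trial.

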**Fig 1 pone.0357906.g001:**
[figure not shown]
Participant timeline: Schedule of enrollment, interventions, and assessments.

**Fig 2 pone.0357906.g002:**
[figure not shown]
Participant Flow Diagram.

Using a 1:1 allocation, we will randomize 90 participants to the BEST intervention (n = 45) or WLC (n = 45). Primary, secondary, and exploratory outcomes will be assessed at baseline, mid-course, and post-intervention (after week 6 of the six-week intervention).

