*Mid-Course Assessment (T2).* At the halfway point of the intervention (week 3), all participants will be emailed a link to complete self-report questionnaires assessing only the primary outcome and the mediator variables. The reduced midpoint battery takes approximately 5–10 minutes to complete.

*Post-Intervention Assessment (T3).* All participants will be emailed the post-intervention assessment link and mailed a second blood collection kit to complete both tasks within 2 weeks following the conclusion of the study intervention. The questionnaire will include all study variables. Assessment burden at post-intervention is equivalent to baseline (approximately 20–30 minutes for questionnaires and 10 minutes for blood collection).

*Procedure for Blood Collection, Processing, and Storage.* The Tasso T-20 device [73] will be used to collect, store, and transport capillary blood for testing at the Social Genomics Core Laboratory. The Tasso is designed for use in non-clinical settings with adult populations. After collection, samples will be stored at −20 °C and analyzed in a single batch once data collection is complete.

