#### Secondary outcomes.

Secondary outcomes include depressive symptoms, burnout, psychological well-being, sleep quality, and markers of inflammation. They will be assessed at baseline (T1) and at the post-intervention time point (T3).

*Depressive symptoms*. Depressive symptoms will be based on scores on the 20-item Center for Epidemiologic Studies-Depression Scale (CES-D), a commonly used depression measure [84]. The CES-D is a reliable, validated, and widely used measure that includes central components of depressive symptomatology [84]. Participants respond to twenty statements that assess how often the individual felt or behaved during the past week on a four-point Likert scale from 0 (rarely or none of the time [less than 1 day]) to 3 (most or all of the time [5–7 days]). All 20 items will be summed to provide a total score. The possible range of scores is 0–60, with higher scores indicating a greater frequency of depressive symptoms. The CES-D has frequently been used to assess depressive symptoms in healthcare workers [29,85] and has been shown to be responsive to mindfulness interventions [86].

*Burnout.* Burnout will be measured via the 22-item Maslach Burnout Inventory for Medical Personnel (MBI-M) [87]. Items assess the frequency of personal attitudes and feelings within the past month [87]. The MBI-M measures three components of burnout: emotional exhaustion, depersonalization, and reduced personal accomplishment. Emotional exhaustion is assessed with nine items and refers to feeling emotionally overextended and exhausted by one’s work. Depersonalization is assessed with five items and refers to an impersonal response toward the recipients of one’s services. Personal accomplishment is assessed with eight items and reflects feelings of competence and achievement in work-related pursuits. All items are scored on a 7-point Likert scale from 0 (never) to 6 (every day). Higher scores on the emotional exhaustion and depersonalization subscales correspond to a greater experience of burnout. The personal accomplishment subscale is positively worded; therefore, a one-item increase corresponds to a greater experience of work-related efficacy. Each subscale will be summed to provide total scores for emotional exhaustion, depersonalization, and personal accomplishment. The MBI-M has been validated in several samples of healthcare workers [88,89] and has been shown to be sensitive to psychosocial intervention effects [90].

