As a complementary, pre-specified sensitivity analysis under a missing-at-random assumption, a linear mixed model will be fit using all available data from all randomized participants with at least one post-baseline observation, with fixed effects for condition and time (categorical) and a random intercept for participants. The between-condition contrast at the post-intervention endpoint will be extracted from this model to correspond to the primary estimand, and change over time and the condition-by-time interaction will be examined as secondary, descriptive analyses [136,137]. As an additional sensitivity analysis, we will repeat the primary outcome models using a per-protocol approach, restricting to participants in the BEST condition who attended at least three of the six intervention sessions (and the corresponding WLC participants), to assess whether the intervention effect differs among those who received the intervention as intended. Since a per-protocol analysis does not preserve the original randomization, it will be interpreted as a complementary, exploratory analysis rather than a confirmatory test of the ITT result. Lastly, because the analyzable sample is modest, the trial is not powered for formal moderation or subgroup analyses. Any examination of whether intervention effects differ across physician subgroups (e.g., specialty) will be exploratory and hypothesis-generating, intended to inform future adequately powered trials rather than to provide confirmatory tests. All tests, primary and secondary outcomes, will be two-sided with an alpha level of 0.05. All analyses will be conducted in R version 4.4.3 [71].

*Mediation analyses.* Mediation analyses will be conducted using the PROCESS macro in R [138]. To enhance the temporal precedence of the intervention’s effect on perceived stress through each mediator, we will assess the outcome (perceived stress) and mediators (compassion, positive emotions, equanimity/mindfulness) for all participants at the midpoint of the six-week intervention (T2). We will fit a parallel mediation model that includes group assignment (BEST vs. WLC) at T1 as the predictor variable, compassion, positive emotions, and equanimity/mindfulness at T2 as the mediators, and PSS scores at T3 as the outcome. The model will control for T1 perceived stress and for each mediator’s T1 values.

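### Two sentences place blood and secondary outcomes at mid-course against the detailed schedule; separately, the mixed-model inclusion rule leaves only T3 completers for those outcomes

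*Protocol article*

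**What the plan says.** **Assessment schedule.** The protocol article describes it in two ways.

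- The abstract (Method) says participants will "provide blood samples at baseline, mid-course, and post-intervention to assess outcomes and mediators". The Methods text below Fig 2 says "Primary, secondary, and exploratory outcomes will be assessed at baseline, mid-course, and post-intervention".
- Under Procedures and study flow, the mid-course visit (T2) consists of "self-report questionnaires assessing only the primary outcome and the mediator variables", and at T3 participants are "mailed a second blood collection kit". Table 1 leaves the T2 cell empty for burnout, well-being, depressive symptoms, sleep, circulating markers and gene expression. It marks T2 for the PSS and the five mediator instruments. The Secondary outcomes section also gives T1 and T3 only.

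**Analysis.** The Data analysis plan makes ANCOVA at T3, adjusted for the T1 value, the main model for every outcome. Missing endpoints are multiply imputed, and data are assumed missing at random given baseline covariates and observed outcomes. A linear mixed model is the complementary sensitivity analysis under the same assumption. It is fitted "using all available data from all randomized participants with at least one post-baseline observation", with condition, categorical time and a random participant intercept. It stands in the part on primary and secondary outcomes and is not limited to the PSS.

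**The concern.** The first issue is a direct contradiction about what is measured at T2 and how many blood samples each participant gives.

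The second does not depend on the first and would remain if those sentences were already correct. A secondary outcome has one post-baseline measurement, at T3. A rule requiring a post-baseline observation of that outcome therefore removes everyone without T3. An analysis described as using all available data under missing at random becomes a completer comparison. It can then differ from the imputed ANCOVA because of who was admitted, and say nothing about whether the imputation was sound.

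**Working it through.** **Part 1: the statements side by side**

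| Place | Secondary outcomes at T2? | Blood samples |
|---|---|---|
| Abstract, Method | Blood: yes | 3 |
| Methods, below Fig 2 | Yes | 3 (inflammation is a secondary outcome) |
| Procedures, T2 and T3 | No | 2 |
| Table 1 | No, all six rows | 2 |
| Secondary outcomes section | No | 2 |

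The three detailed places agree with each other. The two summary sentences are the outliers.

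**Part 2: the mixed model for a T1/T3 outcome**

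Inputs from Sample size: 90 randomized (45 per arm), about 19% attrition, about 72 with complete data, and baseline-post correlation r = 0.50 (range 0.40 to 0.60). The plan gives r for the PSS only; using it for secondary outcomes is an assumption. Also assumed: outcome SD 1 at both visits, and dropouts split evenly (36 completers and 9 dropouts per arm).

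1. *The plan's own figures.* 90 × (1 − 0.19) = 72.9, against about 72 stated. At N = 72 with one covariate, α = 0.05 and 80% power, the noncentral F gives f = 0.335. Then d = 2f√(1 − r²) = 2 × 0.335 × √0.75 = 0.58, as stated. Nothing below alters this.

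2. *Who enters.* At least one post-baseline observation of the outcome means a T3 value, so about 72 enter and 90 − 72 = about 18 do not.

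3. *What is estimated.* A T3-specific contrast needs the condition-by-time term, so it is included here. With T1 and T3 complete for everyone admitted, the contrast equals the raw T3 difference. A simulated data set with 9 dropouts per arm kept exactly 72, and both quantities were -0.6437.

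4. *Precision.* Completers only: SE = √(2/36) = 0.236. With 9 baseline-only participants per arm kept, SE = √[(2/36)(1 − r² × 9/45)]:
   - r = 0.40: √(0.05556 × 0.968) = 0.232
   - r = 0.50: √(0.05556 × 0.950) = 0.230
   - r = 0.60: √(0.05556 × 0.928) = 0.227

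5. *Validity under the plan's assumption.* Illustration: no true effect, r = 0.50, 20% dropout per arm. Dropout is random in the waitlist arm. In the BEST arm it depends on baseline, with dropouts averaging 0.9 SD above the mean at T1.
   - Baseline mean of BEST completers: −(0.20 × 0.9)/0.80 = −0.225 SD.
   - Their expected T3 mean: 0.50 × (−0.225) = −0.11 SD. The waitlist mean is 0, so the completer contrast is biased by about −0.11 SD.
   - With baseline-only participants kept, the joint T1/T3 model adds back 0.50 × 0.225 = 0.11, leaving about 0.
   
   A simulation of this pattern gave about −0.11 under the stated rule, 0.01 with baseline-only participants kept, and −0.01 for ANCOVA.

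**The case against.** *The stakes are low.* This stands. The main analysis of each secondary outcome is ANCOVA with imputation, which keeps all 90. Secondary outcomes are declared exploratory and not powered. The PSS has a T2 value, so its mixed model uses early dropouts who reached T2. The 18 excluded participants would add only a baseline value each, and the standard error shows how little precision that carries.

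*The inclusion rule can be read otherwise.* If any post-baseline measure counts, such as T2 PSS, some dropouts would enter every model with their baseline value. The text does not say so, and outcome by outcome is the natural reading, but the point is conditional on it.

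*Baseline adjustment may be implied.* The plan says that all outcome models adjust for pre-specified covariates. It ties the baseline value specifically to the ANCOVA, however, and names none in the mixed model. If T1 became a covariate, a T1/T3 outcome would have only one time point left, and the categorical time term would have no role.

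*Stronger readings a reader might infer.*
- That the contradiction causes the mixed-model problem, or that the analysis text presumes three visits. It does not: the wording fits two visits or three.
- That staff will send a third blood kit. The operational text is explicit about two.
- That no change over time can be reported. T1-to-T3 change can be, and the analysis plan promises no mid-course trajectory for these outcomes.
- That the registered plan or registry entry is also wrong. Neither is available here.

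**Conclusion.** Both points hold, separately and at modest size.

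The schedule contradiction is certain on the text and rests on no assumption.

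The mixed-model point holds if the inclusion rule is applied outcome by outcome and no baseline covariate is added. The secondary-outcome model then rests on about 72 of 90 participants and returns an unadjusted completer contrast. The issue is validity more than precision: the standard error is 0.236 SD against 0.227 to 0.232. The bias of about −0.11 SD illustrates one dropout pattern that satisfies the plan's assumption and is not a forecast; with dropout unrelated to baseline it would be zero.

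It would go too far to conclude that the secondary results themselves lose 18 participants. Only the sensitivity analysis of exploratory outcomes is touched. The confirmatory PSS test, the imputed analyses and the minimum detectable effect stand.

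**What to change.** 1. Reconcile the two summary sentences with the detailed schedule. If that schedule is the intended one, the abstract could read: questionnaires at baseline, mid-course and post-intervention; blood at baseline and post-intervention. The text below Fig 2 could read: primary outcome and mediators at T1, T2 and T3; secondary outcomes at T1 and T3.

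2. In the Data analysis plan, choose one:
   - for secondary outcomes, drop the post-baseline condition and model T1 and T3 jointly with condition-by-time, so that participants with only a baseline value stay in; or
   - limit the mixed-model sensitivity analysis to the PSS.

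The cost is a few sentences, with no new data or visits. Analysis is planned only after data collection ends, so the change can be made and dated before outcome data are accessed. That matters here because the plan relies on preregistration to offset unblinded analysis.
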